**Methods:**

This randomized controlled trial will assess the efficacy of an 8-week telehealth exercise intervention in 60 patients with multiple myeloma who underwent autologous HSCT (30–180 days post-transplant) and are pre-frail or frail. There will be 30 intervention participants and 30 delayed controls. We will administer remote baseline assessments (week 0), followed by an 8-week telehealth intervention (week 1–8), post assessment (week 9), and an additional follow-up assessment (week 17). Our primary endpoint will be improved physical function, as assessed by the Short Physical Performance Battery test. Our secondary endpoint will be a decrease in frailty characteristics such as gait speed, strength, and fatigue. We will also evaluate the sustainability of improved physical function and frailty at week 17. Participants randomized to the intervention group will perform at least 90 min of exercise per week throughout the 8 weeks.

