Therefore, the purpose of this trial is to evaluate a supervised telehealth exercise intervention (at least 30 min/session × 3 days/week for 8 weeks) that is aimed at improving physical function and frailty in patients with multiple myeloma soon after transplant (30–180 days post-transplant). Our primary outcome is physical function, as assessed by the Short Physical Performance Battery test. Our secondary endpoints are frailty characteristics such as gait speed, strength, and fatigue. We will also evaluate the sustainability of improved physical function and frailty at week 17. We will use an innovative telehealth exercise platform (Moterum Technologies, Salt Lake City, USA) which enables remote exercise interventions (e.g., home-based) that are accessible through digital platforms (e.g., video conferencing on smartphones or tablets) and customizable for users to properly address the individual needs of each participant. We hypothesize that the intervention will improve the Short Physical Performance Battery (SPPB) test and 5-scale frailty index, as objectively ascertained using Bluetooth-enabled biosensors and patient-reported questionnaires, respectively.

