### Eligibility

Eligibility requirements include (1) diagnosed with multiple myeloma; (2) ≥18 years of age; (3) self-reported as pre-frail or frail (i.e., Fried criteria: clinically underweight, exhibiting exhaustion, low energy expenditure, slow walking speed, and muscle weakness), with the presence of 2/5 indices classified as pre-frail and ≥3/5 indices classified as frail; (4) within 30 to 180 days post-HSCT prior to registration; (5) physically able and willing to complete all study procedures; and (6) English-speaking. Patients will be excluded if they (1) have clinically significant/active cardiovascular disease (e.g., unstable angina, uncontrolled arrhythmia, etc.); (2) have contraindications to exercise (acute infectious disease or unstable bone lesions); (3) currently recovering from a recent injury or have been physically injured in the past 6 months, in which participation in rigorous exercise may not be appropriate; (4) self-reported ongoing participation of exercise over 60 min per week; and (5) are female patients who are pregnant or planning to become pregnant. As acknowledged in the manuscript, patients who are frail generally have worse outcomes than those who are not, including worse survival and higher treatment discontinuation rates. However, the optimal timing for interventions to reverse frailty is not known. We have elected to include individuals who are pre-frail, as they may represent an optimal phenotype to target for the long-term sustainability of the intervention, prior to the onset of potentially irreversible physical functional decline. We anticipate that the randomized design of the trial will allow for a balanced allocation of pre-frail and frail study participants between the two arms.

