### Remote measures of physical function and frailty

We will mail gait sensors (for hip, right foot, and left foot), a hand dynamometer, measuring tape, and blue tape to each participant’s home. All of this equipment will be used to assist in measuring physical function and frailty outcomes before and after the intervention at each participant’s home, or remote place of choosing, via live video conferencing. Objective data will be recorded by Bluetooth-enabled sensors into the telehealth exercise platform. All participants will complete an initial 30-min technology support session via Zoom video conferencing, during which research staff will help participants set up their sensors and will verify that the sensors operate properly prior to measuring outcome measures. Frailty will be assessed using a 5-scale frailty index: body mass index, fatigue, level of physical activity, gait speed, and muscular strength. Body mass index will be determined by medical record data while fatigue and level of physical activity will be measured by questionnaires. Gait speed will be collected using gait sensors, and hand dynamometer measurements will be used to assess muscular strength. We will assess physical function remotely using the SPPB under the supervision (through videoconferencing) of study staff. SPPB includes three lower extremity measures completed in the following order: timed balance; gait speed; and chair stand. We will assess timed balance under three conditions: (a) side-by-side stand with both feet placed on the ground for 10 s or when the subject steps out of position; (b) semi-tandem stand with the side of the heel of one foot touching the big toe of the other foot for 10 s or when the subject steps out of position; and (c) tandem stand with the heel of one foot touching the big toe of the other foot for 10 s or when the subject steps out of position. We will assess gait speed by instructing participants to measure and mark a 4-meter flat surface distance, across which they will be asked to walk at their “usual” pace. Next, participants will be asked to walk at their “usual” pace to cover the 4-meter distance once more. Time will be recorded using an electronic timer, and the fastest time will be documented. We will assess chair stand under two conditions — participants will (a) perform a single chair stand and (b) be asked to perform five repeated chair stands as quickly as possible; time to completion will be recorded. All participants will complete the remote physical assessments on week 0, week 9, and week 17.

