### Statistical analysis

We will generate descriptive statistics for participants’ demographics, lifestyle behaviors (physical activity, tobacco use), family history of chronic disease, history of other comorbidities (e.g., hypertension, diabetes, dyslipidemia, thyroid disease), and cancer treatment-related exposures. We will assess participation bias by comparing demographics (age, gender, race/ethnicity) and treatment-related exposures among participants and non-participants. Although the number of adverse events is not the major outcome of the study, we will report any adverse events during the study intervention period. We will use a two-sided type I error=0.05. An intention-to-treat analysis will be done by including all randomized participants. We will also conduct another analysis by excluding participants that demonstrate <70% compliance rates within the telehealth exercise sessions completed (17/24). *Hypothesis 1*: The intervention will improve the SPPB test, as objectively measured using Bluetooth-enabled biosensors. We will assess changes in physical function from baseline to week 9 by using the Generalized Estimation Equation (GEE) model with an indicator variable of time, accounting for within-person correlations in measurements. Treatment by time interaction will be included in GEE and its significance tested to assess treatment effects. Body mass index, age, and race will be determined through medical records and included in GEE as a priori covariates for adjustment. Changes in physical function measures from baseline to week 9 will also be examined by a paired *t*-test (within the treatment group). A 2-sided significance level of *p*<0.05 will be used. *Hypothesis 2*: The intervention will improve a 5-scale frailty index, as measured by patient-reported questionnaires. We will assess group differences in changes in the proportion of participants who are of pre-frail or frail from baseline to week 9 using the GEE approach for proportions, accounting for correlation between measurements. As in hypothesis 1, we will include the same covariates for adjustment in the analysis. *Hypothesis 3*: Intervention-related improvements in physical function and frailty will be sustained at week 17. We will examine the long-term effects of the telehealth exercise intervention by fitting GEE models for the outcomes at weeks 9 and 17. The model will include the treatment main effect (to allow for group differences at week 17), time, and the treatment group by time interaction. Contrasts will be used to test if the group difference at week 17 equals that at week 9. As in hypothesis 1, we will include the same covariates for adjustment. Additionally, between-group differences in outcome values at week 17 will be computed, along with 95% confidence intervals, and compared to the differences at week 9. Linear mixed-effects modeling will be used to evaluate the effect of interventions over time on the primary and key secondary outcomes. The models incorporate subject-specific random effects to account for within-subject correlation due to repeated measures. Group averages, as well as subject-specific intercepts and slopes, will be estimated to capture potential variations in the baseline values and slopes among individuals. Linear mixed-effects models accommodate missing data due to dropout, such that all randomized participants can be included. We will compare participants who complete the study with those who do not and identify potential factors that are associated with dropout. An interim analysis is not currently planned for this study.

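### The secondary endpoint is stated as frailty characteristics and a five-item index, but the only formal frailty test is pre-frail-or-frail status, which nearly every participant has at entry

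*Protocol article*

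**What the plan says.** The protocol article describes the frailty outcome in three ways.

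- **Characteristics.** Abstract, Methods: "Our secondary endpoint will be a decrease in frailty characteristics such as gait speed, strength, and fatigue". Background: "Our secondary endpoints are frailty characteristics such as gait speed, strength, and fatigue".
- **Index.** Background, as the study hypothesis: "We hypothesize that the intervention will improve the Short Physical Performance Battery (SPPB) test and 5-scale frailty index". The section on remote measures defines it: "Frailty will be assessed using a 5-scale frailty index: body mass index, fatigue, level of physical activity, gait speed, and muscular strength".
- **Status.** Statistical analysis, Hypothesis 2, names the index but then specifies the test as: "We will assess group differences in changes in the proportion of participants who are of pre-frail or frail from baseline to week 9".

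The Eligibility section sets the categories, "with the presence of 2/5 indices classified as pre-frail and ≥3/5 indices classified as frail", and requires one of them, by self-report, for entry. Later in Statistical analysis comes: "Linear mixed-effects modeling will be used to evaluate the effect of interventions over time on the primary and key secondary outcomes". The article does not list the key secondary outcomes. The Discussion says that showing frailty held steady rather than worsening, relative to control, would be clinically important.

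**The concern.** The one frailty test that the article fixes does not follow the endpoint that it states. Gait speed, strength and fatigue are measured by sensor, dynamometer and the 13-item FACIT-fatigue scale, yet no analysis names them. The index is tested only after reduction to a yes/no status.

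The two can disagree. A participant who improves on all three measures without crossing item cut-offs is a gain under the Abstract and Background, and no change under Hypothesis 2. A participant whose count falls from 2 to 1 through body mass index or activity is the reverse.

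At stake is the trial's conclusion on frailty. With more than one candidate outcome and two model types (GEE for proportions, linear mixed model), the result could depend on which is put forward. The status is also a blunt measure in a population selected for having it.

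**Working it through.** **Step 1. Does any analysis name the stated characteristics?** Hypothesis 1 concerns the SPPB. Hypothesis 2 concerns the proportion pre-frail or frail. Hypothesis 3 carries physical function and frailty to week 17. The mixed-model sentence refers to unnamed key secondary outcomes. None names gait speed, strength or fatigue as an outcome.

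**Step 2. What can the status show?** Entry requires at least 2 of 5 indices, so the baseline proportion is near 100% in both arms. It may be somewhat lower when measured, because eligibility is self-reported. The difference in changes then reduces to the difference at week 9. A fall from 4 items to 2 (frail to pre-frail) and a rise from 2 to 4 (pre-frail to frail) both count as no change. The second is the worsening that the Discussion hopes to show is avoided.

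**Step 3. Inputs for power.** The plan has no frailty power figure to reproduce: its power statement covers physical function only.

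- Evaluable per arm: 30 × (1 − 0.20) = 24 (Power calculations).
- Baseline to week-9 correlation: 0.8 (Power calculations, which also mention 0.70 and 0.9).
- Significance level: "We will use a two-sided type I error=0.05".
- Assumed, not in the documents: a 0.5 SD gain in each of gait speed, strength and fatigue; no gain in body mass index; an activity gain of 0 to 1.5 SD; inter-item correlation 0.3; item prevalences of 50, 50, 60, 60 and 10%, or 35, 35, 50, 70 and 5% (gait, strength, fatigue, activity, body mass index).

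**Step 4. Hand check with activity unchanged.** Under the first prevalence set, the simulated week-9 proportions are about 86% (control) and 68% (exercise).

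- Pooled p = 0.77. Null SE = √(2 × 0.77 × 0.23 / 24) = 0.1215.
- Alternative SE = √((0.86 × 0.14 + 0.68 × 0.32) / 24) = 0.1187.
- z = (0.18 − 1.96 × 0.1215) / 0.1187 = −0.49, so power is about 31%.

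For one continuous measure adjusted for baseline:

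- Residual SD = √(1 − 0.8²) = 0.6. SE = 0.6 × √(2/24) = 0.173.
- z = 0.5/0.173 − 1.96 = 0.93, so power is about 82%.

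**Step 5. Simulation over the activity gain.** Simulated participants entered with at least 2 of 5 deficits. The status was compared by a two-sample test of week-9 proportions, as a stand-in for the planned GEE. The continuous measure and the count were each compared by baseline-adjusted regression.

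| Activity gain | Yes/no status | Index as 0–5 count | One continuous measure |
|---|---|---|---|
| 0 | 31–32% | 54–58% | 77–82% |
| 0.5 SD | 54–56% | 75–77% | 77–82% |
| 1.0 SD | 72–79% | 91–92% | 77–82% |
| 1.5 SD | 82–92% | 97–98% | 77–82% |

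Figures are approximate. Repeat runs and further prevalence sets put the first status figure at 30–41%. The count had more power than the status in all 12 settings run.

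**Step 6. What the status needs.** With 24 per arm, 80% power requires an absolute difference of about 33 percentage points if the control rate is 95%, rising to about 40 points if it is 70%.

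**The case against.** A reader might infer that Hypothesis 2 tests a wholly different endpoint, with less than half the power. The documents support neither part.

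- **A different endpoint.** The phrase "such as" marks the three characteristics as examples, all three are items of the index, and the Background itself hypothesises on the index. What stands is narrower: characteristics, index and status are not tied together, and improving an index is not the same as leaving the category pre-frail or frail.
- **Less than half the power.** This holds if physical activity does not change. Yet the Eligibility section excludes people exercising over 60 minutes a week, the intervention asks for at least 90, and activity is an index item. At an activity gain of 1.5 SD the status equals or exceeds one continuous measure. The size of that gain is itself unknown, and the article concedes that the activity questionnaire may miss small changes. Other ways of linking a 0.40 SD effect to the status give power ratios from 0.12 up to 0.77. No single ratio can be claimed, nor can it be said that real gains would usually be missed.
- **No test at all for the named measures.** This is too firm. A linear mixed model suits continuous measures better than a yes/no status, so the mixed-model sentence may be meant to cover them. A list of key secondary outcomes may also sit in a full protocol or SAP that is not shown. What stands is that the article fixes the Hypothesis 2 test, and that test uses the status alone.

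Replacing the index with the three measures would also go too far, because the index is a stated hypothesis.

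**Conclusion.** The mismatch is real and rests on the text alone. The stated secondary endpoint is characteristics of frailty, and the stated hypothesis is improvement in the index. The formal test is a category that eligibility fills almost completely at baseline and that cannot register movement between its two levels.

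The effect on power is not fixed by the documents. With 24 per arm, correlation 0.8 and 0.5 SD gains in the three named measures, the status ranges from about 31–32% to 82–92% as the assumed activity gain goes from 0 to 1.5 SD, against about 77–82% for one continuous measure. The firmer comparison is status against count: the same five items scored 0–5 had more power in every setting run. The point concerns a secondary outcome and leaves the primary SPPB analysis untouched, but the trial's claim about frailty depends on it.

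**What to change.** In Statistical analysis:

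1. State that the key secondary outcomes are week-9 gait speed, grip strength and FACIT-fatigue score on their continuous scales, each adjusted for its week-0 value and the planned covariates, with a multiplicity adjustment such as Holm.
2. Under Hypothesis 2, test the five-item index as a 0–5 count adjusted for its baseline value, and say whether this test belongs to the same multiplicity family.
3. Report pre-frail/frail status as supportive.
4. Use the same definitions in the Abstract, the Background and Hypothesis 3.

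The cost is wording. The physical measures and questionnaires are already scheduled at weeks 0, 9 and 17, and the count needs nothing that the status does not already need. The category result becomes less prominent, and the adjustment costs some power. At the strictest step (0.05/3, critical value 2.394), one continuous measure in the hand check above has z = 2.887 − 2.394 = 0.49, or about 69% power. The chance that at least one of the three is significant at that level was 88–92% in simulation, under the 0.5 SD and 0.8 assumptions.

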## Methods/design

A single-center, investigator-blinded randomized, parallel-group, superiority study was conducted to demonstrate the efficacy of a telehealth exercise intervention on physical function and frailty in patients with multiple myeloma who received HSCT at City of Hope (COH). Figure 1 depicts the flow of the study. We will conduct an 8-week telehealth intervention that will include baseline (week 0) and post-intervention measures (week 9, week 17) on physical function and frailty measures. We will randomize 60 pre-frail or frail patients with multiple myeloma (1:1) to either the 8-week telehealth exercise intervention group (*n*=30) or the delayed control group (*n*=30). All study procedures, including screening and enrollment, will be performed using a telehealth-based approach and will not require participants to be assessed at a clinical center.

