### Prescreening/screening

The long-term follow-up after hematopoietic cell transplant program at COH ensures the active and comprehensive follow-up of all patients who have undergone transplant at COH since 1976 — capturing demographics, disease, and vital status, as well as post-transplant complications such as new malignancies, cardiopulmonary disease, and endocrinopathies. Based on our database, we will prescreen all patients diagnosed with multiple myeloma, who will undergo the transplant at COH. After identifying potentially eligible patients, we will inform their primary hematologist at COH to confirm the physician’s clearance before contacting the eligible patients. Each potentially eligible patient will be contacted by phone to determine the patients’ willingness to participate and to identify patient-reported pre-frailty or frailty. If potentially eligible patients do not respond to our initial contact, we will call up to 3 more times, and discontinue our efforts if there is no response. These individuals will be deemed as non-responders

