Although this study will provide the first evidence of a novel telehealth exercise approach targeting frailty and physical function in patients with multiple myeloma, it is beyond the scope of the current study to elucidate the mechanisms of improving frailty with exercise. Our study has the potential to demonstrate that frailty is maintained and not worsened during the intervention when compared to the delayed control group, which will be a clinically important finding. We recognize that poor retention is a possibility, given the time and effort needed to partake in an intervention study. Therefore, we have accounted for a 20% attrition rate (from randomization to week 17 post-intervention). This takes into consideration patient death, recurrence of cancer, illness, or loss to follow-up. We acknowledge that there may be differential loss to follow-up according to participant attributes and prognosis, which may contribute to participation bias and/or survival bias. To minimize participation bias, we will incorporate many of the strategies (e.g., reminders, incentives) that we have successfully used to maintain excellent participation rates in our exercise intervention studies to date. Attrition will be monitored in real time, allowing us to address obstacles in a timely manner. Differential loss to follow-up due to prognosis, death, and missing data will be addressed using statistical methods of pattern mixture models and multiple imputation. Finally, recruitment of patients with multiple myeloma can be challenging. However, our ongoing successful recruitment strategies in place for the current study, which includes collaborating with the hematology team at COH, appear to be a successful recruitment plan.

This study will provide critical evidence that contributes to the development of comprehensive telehealth exercise programs in HSCT survivors by investigating the effects of an 8-week telehealth exercise intervention in HSCT survivors with the potential of demonstrating improvements and sustainability in physical function. If successful, our approach would be low cost, easily disseminated, and have potential implications for the management and prevention of frailty in HSCT survivors as well as other cancer survivors at risk of developing frailty after cancer treatment.

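### Hypothesis 2 analyses change in a proportion that eligibility holds at or near 100% at baseline, and the pooled outcome cannot register movement between pre-frail and frail

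*Protocol article*

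**What the plan says.** All of this is in the protocol article.

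- **Entry.** Under Eligibility, patients must be "self-reported as pre-frail or frail", "with the presence of 2/5 indices classified as pre-frail and ≥3/5 indices classified as frail". Patients with 0 or 1 of the 5 indices do not qualify. Prescreening/screening uses a telephone call "to identify patient-reported pre-frailty or frailty". Methods/design describes all 60 randomized patients (30 per arm) as pre-frail or frail.
- **Outcome and model.** Under Statistical analysis, Hypothesis 2: "We will assess group differences in changes in the proportion of participants who are of pre-frail or frail from baseline to week 9". The method is a GEE for proportions with the same covariates as Hypothesis 1 (body mass index, age, race). No link function is named. Hypothesis 1 tests the treatment-by-time interaction, and a group difference in change is the same contrast.
- **Measurement.** Hypothesis 2 reads: "The intervention will improve a 5-scale frailty index, as measured by patient-reported questionnaires". Remote measures of physical function and frailty says otherwise for two of the five components: "Gait speed will be collected using gait sensors, and hand dynamometer measurements will be used to assess muscular strength". Body mass index comes from the medical record; only fatigue and physical activity come from questionnaires.
- **Aim.** The Discussion says the trial may show that "frailty is maintained and not worsened during the intervention when compared to the delayed control group", and calls this clinically important.

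**The concern.** The entry criterion and the baseline outcome are the same classification. A change from baseline is informative only if baseline can vary, and here the design removes nearly all of that variation.

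Two consequences follow. First, whether the model can be fitted depends on a link that is not named and, under a logit link, on whether at least one patient in each arm happens to score below 2/5 at week 0. Second, combining pre-frail and frail into one state hides every move between them. A patient who goes from 2/5 to 4/5 counts as unchanged, and so does one who goes from 4/5 to 2/5. What is at stake is the test of the frailty hypothesis and any statement about non-worsening that rests on it.

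**Working it through.** The article gives no frailty rate, effect size or power for Hypothesis 2, so there is no stated figure to reproduce. The week-9 counts below are assumptions chosen to show how the model behaves.

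**Inputs**
- 30 per arm (Methods/design) and 20% attrition to week 9 (Power calculations): 30 × 0.80 = 24 per arm.
- Baseline pre-frail or frail: 24/24 in each arm (from Eligibility).
- Week 9, assumed: control 20/24 = 0.833; exercise 14/24 = 0.583.
- Model: GEE with treatment, time and treatment × time, clustered by patient, robust SE.

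**Step 1: what the change contrast is.** On the proportion scale the contrast is (p_ex,9 − p_ex,0) − (p_con,9 − p_con,0). With both baselines equal to 1 it becomes p_ex,9 − p_con,9, the week-9 difference.

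**Step 2: identity link.** Difference: 0.583 − 0.833 = −0.25. SE = √(0.833×0.167/24 + 0.583×0.417/24) = 0.126. The fitted GEE interaction is −0.25 (SE 0.126), identical to the week-9-only analysis. With 30/30 at baseline and assumed 24/30 against 18/30 at week 9, it is −0.20 (SE 0.115).

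**Step 3: log link.** ln(0.583/0.833) = −0.357. SE = √((1 − 0.583)/14 + (1 − 0.833)/20) = 0.195. The GEE gives the same values, again the week-9 comparison.

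**Step 4: logit link.** The baseline log odds are ln(24/0), which is infinite. The software stops at an intercept of 25.6. The interaction SE is 111.6 under independence and undefined under exchangeable correlation. These values depend only on where the iterations stop; the finding is that no usable test results. A logistic model of week 9 alone is well behaved: ln[(14/10)/(20/4)] = −1.273, SE = √(1/14 + 1/10 + 1/20 + 1/4) = 0.687.

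**Step 5: measured baseline slightly below 100%.**

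| Week-0 pre-frail or frail (control, exercise) | Logit interaction | SE |
|---|---|---|
| 24/24, 24/24 | −1.273 | 111.6 or undefined |
| 23/24, 24/24 | diverges | about 10⁶ or undefined |
| 22/24, 22/24 | −1.273 | 0.894 |

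One arm at 100% is enough to break the logit model. The 0.894 also depends on how baseline and week-9 status are paired within patients in the constructed data.

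**Step 6: what the outcome can register.** Score 1 for 2/5 or more, 0 otherwise. Then 2/5 → 4/5 is 1 → 1, and 4/5 → 2/5 is 1 → 1. Only crossing from 2 or more to 0 or 1 changes the outcome. This holds under every link.

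**The case against.** The strongest reply is that the hypothesis can still be tested. A reader might infer from the logit result that Hypothesis 2 is not estimable as written. The article does not support that: it names no link, an article may leave that detail to the analysis plan, and a difference in changes of proportions sits naturally on the identity scale, where the estimate is finite. Hypothesis 3 also already fits GEE models to the outcomes at weeks 9 and 17 without baseline rows, so a week-9 frailty contrast can be obtained from a planned model. All of this stands. It shows, however, that the workable analysis is the week-9 comparison, which the article does not name as the Hypothesis 2 test.

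Baseline may also fall below 100%. Entry rests on a telephone self-report, whereas the week-0 index includes measured gait speed and grip strength, so some patients could score 0 or 1 of 5. That stands too, but testability under a logit link would then depend on such patients turning up in both arms. A reader might go further and infer that the change from baseline partly reflects a switch from self-report to measurement. If baseline is the week-0 assessment, the same remote measurements are planned at weeks 0, 9 and 17 and no switch occurs.

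Finally, a reader might infer that the trial cannot see worsening at all. That is too strong. Gait speed, strength and fatigue are named secondary endpoints, linear mixed models are planned for key secondary outcomes, and the Discussion sentence is not tied to the Hypothesis 2 test. The limit applies to this endpoint only.

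**Conclusion.** The point holds in a limited form and should be fixed. Eligibility puts the Hypothesis 2 proportion at or very near 100% at baseline. A logit-link interaction then has no usable standard error if either arm is at 100%, and an identity or log link gives the week-9 comparison when both arms are. Independently of the link, the pooled outcome cannot register movement between pre-frail and frail, so by itself it cannot support a claim that frailty did not worsen; the component endpoints may inform that question.

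The exact 100% assumes that week-0 status agrees with the screening self-report. The numerical examples rest on assumed week-9 counts, so they show the model's behaviour and not the trial's expected effect or power. This is a secondary hypothesis; the primary SPPB analysis is untouched. The description of the index as questionnaire-measured is a separate, editorial inconsistency.

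**What to change.** 1. Define the Hypothesis 2 test as a week-9 between-arm comparison of the 0-5 frailty count, adjusted for the week-0 count and the covariates already listed. An ordinal model of not frail, pre-frail and frail, adjusted for week-0 category, is an alternative. Choose one in advance.
2. Report the week-9 proportion no longer pre-frail or frail by arm, with the risk difference and its 95% CI.
3. State that baseline status is the week-0 assessment. Correct the Hypothesis 2 wording, and the matching sentence that closes the Background, so that gait speed and grip strength are the device-measured values described under Remote measures of physical function and frailty.
4. Rest any statement about non-worsening on the count, the ordinal category or the component endpoints, not on the pooled proportion.

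The cost is wording only: all five components are already part of the planned index, so no new data are needed. The downside is small. A count or ordinal result is less directly read as reversal of frailty, and the risk difference in item 2 covers that.
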